### Main study parameter/endpoint efficacy {12}

The combined incidence of all TEC and all-cause mortality within 30 days or during the same admission in hospital, compared between ACT-guided heparinization and a bolus of 5000 IU of heparin. TEC are any complication as caused by thrombus or embolus perioperatively, including but not exclusively myocardial infarction, leg ischemia, deep venous thrombosis, colon ischemia, TIA/stroke, graft thrombosis, peroperative thrombus requiring embolectomy or re-do of an anastomosis, thrombus or embolus in organs or lower limbs, and other peripheral thromboses. The statistical efficacy analysis will be conducted with a chi-square test for proportions. Differences in the incidence of this composite endpoint between the intervention and control groups will be expressed as the absolute risk difference with a 95% confidence interval.

### Main study parameter/endpoint safety {12}

Incidence of bleeding complications according to E-CABG classification, grade 1 and higher: per- or postoperative transfusion of 2 or more units of red blood cells, transfusion of platelets, transfusion of fresh frozen plasma, or re-operation for bleeding during the hospital stay [30, 31]. For the bleeding complications, a non-inferiority test will be used. This will be tested using a one-sided *t* test with an alpha of 0.025.

### Secondary study parameters/endpoints {12}

Secondary endpoints: complications (non-TEC), within 30 days postoperative or in the same admission, as defined by DSAA and suggested standards for reports on aneurysmal disease: all complications requiring re-operation, longer hospital stay, and all other complications; incidence of kidney injury as defined by RIFLE criteria: rise of serum creatinine > 100% or decrease of eGFR with 50% [35]; allergic reactions; ACT values (in the intervention group), total heparin administration, and protamine administration; peroperative blood loss, blood transfusions either autologous or homologous, other blood product administration, total operative time, aortic clamping time, use of adjunctive hemostatic products, and length of hospital (including ICU) stay; health status as measured with the EQ-5D-5L; and economic and health care cost evaluation by IMCQ and IPCQ and addition of out-of-pocket expenses.

### Other study parameters {12}

#### Preoperative parameters

Patient demographics: sex, smoking history, body length and weight and body mass index, medical history (general, cardiac, pulmonary, diabetes, surgical), medication, all previous vascular interventions; blood pressure and pulse at the outpatient visit, ECG reports; diameter and anatomical classification of abdominal or iliac aneurysms; preoperative laboratory results: Hb, leucocytes, sodium, potassium, creatinine, eGFR, platelets; presence of impaired renal function (eGFR < 40 ml/min).

#### Peroperative parameters

Epidural analgesia; surgical approach; clamping sites at arteries.

### Ethical considerations

If patients meet the inclusion criteria, they will be fully informed about the trial and provided with a patient information form and have the opportunity to ask questions. Patients willing to participate will sign the informed consent form. This study will be conducted in accordance with the Good Clinical Practice (GCP) guidelines, with the principles of the Declaration of Helsinki, and with the Medical Research Involving Human Subjects Act (WMO). The medical ethical committee in Amsterdam (2019.732 – NL6675902919) has approved the study protocol, as well as local institutional boards of each participating center. All legal European demands concerning insurances for possible harm from trial participation are met and all separate trial study sites have insurance as legally demanded by the Dutch Government for non-trial harm for participating patients {30}.

### Safety and quality control

#### Independent Central Adjudication Committee

The ICAC is instituted to decide whether complications are rightfully labeled as TEC in the CRF. Two vascular surgeons and 1 registered intensive care specialist will form this committee, none of them being a member of the ACTION-1 project group.

This committee will gather 30 days after 100, 200, and 500 inclusions and 6 weeks after the last inclusion. They are blinded for the intervention and will judge the complication parts of the CRFs of all included patients.

In case of disagreement within this committee, the majority will be decisive. In case this committee decides that they need further clarification on a specific complication, this will be provided by the project group with data from the original electronic patient file of the patient.

### Data Safety Monitoring Board {21 a,b}

Despite the fact that this study is labeled as moderate risk, a full DSMB is installed. The DSMB is composed of three independent experts: a vascular surgeon, a cardio-thoracic surgeon, and a clinical epidemiologist and biostatistician.

A safety review will be performed by an independent statistician ([name], PhD) and reviewed by the data safety monitoring committee after the results are available for 100, 200, and 500 patients. This is a safety review, which looks at the combination of several outcomes as opposed to a traditional interim analysis with specified stopping rules.

In case of strong concerns about safety, the safety monitoring committee can advise to stop the study. Furthermore, serious adverse events (SAEs) will be reported to the data and safety monitoring committee.

A total of three safety reviews are planned:
A first interim analysis is planned when approximately 100 subjects have been enrolled. This will provide data sample size calculations and safety assessments.A second interim analysis is planned when approximately 200 subjects have been enrolled. This will provide data sample size calculations and safety assessments.A third interim analysis is planned when approximately 500 subjects have been enrolled. This will provide data sample size calculations and safety assessments.

Additional ad hoc interim analyses may be conducted to support decision-making concerning the current clinical study, the sponsor’s clinical development projects in general or in case of any safety concerns.

Independent personnel who are not directly involved in conducting the study will perform the interim analyses and review of the unblinded outputs.

The DSMB should consider stopping the study if the following conditions are met:

The stopping rule for safety is:
A difference in all-cause mortality within 30 days after surgery or during the same admission between intervention and control groups with *P* value smaller than 0.05 in disadvantage of the intervention groupA difference in life-threatening bleeding (E-CABG classification grade 2 or higher: transfusion of 5 or more units of red blood cells or re-operation for bleeding) between the intervention and control groups with a *P* value smaller than 0.05 in disadvantage of the intervention groupA difference in the composite of all-cause mortality or life-threatening bleeding (E-CABG classification grade 2 or higher: transfusion of 5 or more units of red blood cells or re-operation for bleeding) between the intervention and control groups with a *P* value smaller than 0.05 in disadvantage of the intervention group

Stopping rules for efficacy:

The DSMB should only under exceptional circumstances advise to terminate the trial under overwhelming efficacy of the ACT-guided heparin group over the control group: the DSMB could consider stopping when a difference in the incidence of TEC and mortality within 30 days after surgery or during the same admission between the intervention and control groups with a *P* value smaller than 0.001 occurs, according to Haybittle–Peto boundary.

No further dissemination of interim results should occur, in particular not with individuals involved in treating the study’s subjects or assessing clinical data.

While monitoring guidelines have been provided, the DSMB uses all available evidence and its collective judgment to base its recommendation to stop or modify the study.

### Adverse, severe adverse events, and suspected unexpected serious adverse reactions {22}

Adverse events are defined as any undesirable experience occurring to a subject during the study, whether or not considered related to the intervention. All adverse events, within 30 days postoperative or in the same admission, reported spontaneously by the subject or observed by the investigator will be recorded. During all procedures in ACTION-1, one of the trained team members will be present in the operating room during the duration of the entire procedure. This team member will complete the peroperative variables in the electronic CRF. After 30 days, the electronic patient file will be checked for complications, and the eCRF will be completed. All AEs and SAEs will be systematically recorded.

A SAE is defined as any untoward medical occurrence or effect that results in death, is life threatening (at the time of the event), requires hospitalization or prolongation of existing inpatients’ hospitalization, and results in persistent or significant disability or incapacity, or any other important medical event that did not result in any of the outcomes listed above due to medical or surgical intervention but could have been based upon appropriate judgment by the investigator. An elective hospital admission will not be considered a serious adverse event.

All SAE will be reported by the local principal investigator to the sponsor within 24 h of the study site staff becoming aware of the event. The sponsor will report all the SAE in a line listing, which will be reported once every 6 months to the medical ethical committee.

Adverse reactions are all untoward and unintended responses to an investigational product related to any dose administered. Unexpected adverse reactions are suspected unexpected serious adverse reactions (SUSARs) if the following three conditions are met: the event must be serious; there must be a certain degree of probability that the event is a harmful and an undesirable reaction to the medicinal product under investigation, regardless of the administered dose; and the adverse reaction must be unexpected, that is to say, the nature and severity of the adverse reaction are not in agreement with the product information as recorded in the summary of product characteristics.

All SUSARs will be reported by the sponsor to the DSMB and to the accredited medical ethical committee via “Toetsingonline” on the website of the Central Committee on Research involving Human Subjects (CCMO, www.ccmo.nl).

Independent monitoring and extensive quality control including all extensive legal demands for major trials with pharmaceuticals are met by an international acclaimed bureau: Julius Clinical (https://www.juliusclinical.com).

All pre-specified AEs and SAEs will be collected and reported in trial publications.

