### Data collection and management {18 a,b, 19}

After 30 days, all postoperative variables will be collected into the electronic database. All study parameters are standard care and can be reproduced from electronic patient files. Extensive standard operating procedures (SOP) are present to secure that data is properly scored.

All data will be collected at each participating center using the eCRF in the electronic database Castor EDC. Castor complies with all applicable laws and regulations with regard to ICHG GCP and the General Data Protection Regulation (GDPR). Each participating center will maintain a key list. This key list stays in the local hospital and will not be shared. After completion of the study, all study documents will be stored on site for 25 years.

All participating sites will be monitored by a Clinical Research Associate (CRA) of the sponsor Dijklander ziekenhuis and a selection site by a monitor of Julius Clinical, a Clinical Research Organization (CRO) {27}.

After completion of the trial, all raw data will be made available for others, following the mandatory policy of ZonMw. No contractual agreements are made that limit any access for other investigators {29}.

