### Patient outcome analysis

Patients will be asked to complete the EQ-5D-5L health status questionnaire at baseline, 1 week, 4 weeks, 13weeks, and 26 weeks after surgery. These forms can be completed online or at home by the patients and send to the investigators by post. These questionnaires will be included in the CRFs. The EQ-5D-5L scoring profiles can be converted into a health utility score based on general population-based Dutch tariffs [37]. QALYs will be calculated for each patient using linear interpolation between the successive health utility assessments over time.

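### After surgery, the only active search stated for primary-endpoint events is a patient-file check after 30 days, so non-fatal TEC treated elsewhere after discharge can be missed

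*Protocol article*

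**What the plan says.** **Endpoint.** *Main study parameter/endpoint efficacy* defines the outcome as "The combined incidence of all TEC and all-cause mortality within 30 days or during the same admission in hospital". TEC is broad: it includes myocardial infarction, deep venous thrombosis, TIA/stroke, leg and colon ischaemia and other peripheral thromboses. The effect is reported as an absolute risk difference with a 95% confidence interval.

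**How postoperative events are found.** The adverse-event section says: "After 30 days, the electronic patient file will be checked for complications, and the eCRF will be completed". *Data collection and management* repeats the timing, "After 30 days, all postoperative variables will be collected into the electronic database", and names the source and place: "All study parameters are standard care and can be reproduced from electronic patient files" and "All data will be collected at each participating center using the eCRF in the electronic database Castor EDC". *Follow-up and quality of life measurements* leaves outpatient visits to local protocols.

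**Other routes.** A trained team member is in the operating room throughout and enters the peroperative variables. The adverse-event section also states: "All adverse events, within 30 days postoperative or in the same admission, reported spontaneously by the subject or observed by the investigator will be recorded". SAEs go to the sponsor within 24 hours, counted from the moment site staff learn of them.

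**Adjudication.** The blinded committee judges the complication parts of all patients' CRFs. If it needs clarification on a specific complication, it receives data from the original patient file.

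**Contact with patients.** *Patient outcome analysis* has the EQ-5D-5L completed "at baseline, 1 week, 4 weeks, 13weeks, and 26 weeks after surgery", online or by post. Medical-consumption (iMCQ) and productivity questionnaires follow later.

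**The concern.** A complication that never reaches the file consulted, and is neither observed by the investigator nor volunteered by the patient, is not missing data. It is a recorded non-event. The rule that excludes subjects with missing data therefore does not apply to it. Adjudication can reclassify what was entered, but the article gives it no route to what was not. The exposed events are non-fatal TEC after discharge that a GP or another hospital handles, such as a deep venous thrombosis or a TIA.

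The protocol takes this into account for costs but not for the primary endpoint. *Cost analysis* draws hospital care from CRFs and hospital systems, and asks the patient about care outside the hospital. No comparable step is stated for finding TEC.

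Two things are at stake. Under-capture that is equal in both arms leaves the ratio of TEC rates intact but shrinks the absolute difference, which is what the trial reports and is sized on. In addition, the patient is fully blinded, and *Discussion* acknowledges that surgeons may hold strong beliefs about their own regimen. A structured question to the patient would add a blinded source for the period after discharge.

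**Working it through.** **Inputs** (all from *Sample size calculation*): TEC 14% against 8%; mortality 5% against 3%; composite 19% against 11%, which is the plan's own addition of the two components; continuity-corrected chi-square test, two-sided alpha 5%, power 80%; 337 per group; 10% dropout; 750 in total.

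**1. The plan's figure.** With mean rate p̄ = 0.15 and difference d = 0.08:

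n₀ = [1.960·√(2·0.15·0.85) + 0.842·√(0.19·0.81 + 0.11·0.89)]² / 0.08² = 311.5, or 312 rounded up.

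With the continuity correction, n = (n₀/4)·[1 + √(1 + 4/(n₀·d))]², which gives 337 after rounding up. Then 337/0.9 = 374.4, so 375 per group and 750 in total. The stated figures reproduce.

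**2. Power at 337 per group.** Power = Φ{[d − 1/n − 1.960·√(2p̄(1−p̄)/n)] / √[(p₁(1−p₁) + p₂(1−p₂))/n]}.

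With full capture: (0.0770 − 1.960·0.02751)/0.02733 = 0.846, so power is 80.1%. There is no reserve.

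**3. Under-capture of TEC only.** Deaths are taken as complete. Let s be the share of TEC captured, equal in both arms. The article gives no value, so s is an assumption shown as a range. The observed rates are p₁ = 0.14s + 0.05 and p₂ = 0.08s + 0.03.

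| TEC missed | Observed rates | Difference (points) | Power at 337 | n per group for 80% |
|---|---|---|---|---|
| 0% | 19.0% / 11.0% | 8.0 | 80.1% | 337 |
| 5% | 18.3% / 10.6% | 7.7 | 78.2% | 352 |
| 10% | 17.6% / 10.2% | 7.4 | 76.1% | 369 |
| 15% | 16.9% / 9.8% | 7.1 | 73.9% | 387 |
| 20% | 16.2% / 9.4% | 6.8 | 71.6% | 407 |

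**4. Only a post-discharge share exposed.** Suppose a share f of TEC occurs after discharge and a fraction m of those is missed, so s = 1 − f·m. Both values are assumptions.

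| f | m | TEC missed overall | Difference (points) | Power |
|---|---|---|---|---|
| 10% | 10% | 1% | 7.94 | 79.7% |
| 10% | 50% | 5% | 7.7 | 78.2% |
| 20% | 50% | 10% | 7.4 | 76.1% |
| 30% | 50% | 15% | 7.1 | 73.9% |

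**5. Window against check.** The endpoint and the adverse-event recording rule share one window: 30 days or the same admission. The file check is placed after 30 days, with no upper limit and no statement on patients who are still in hospital then. The two fit together if the complication section is completed at discharge for those patients. The article does not say this.

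**The case against.** **The file check is not the only route.** A reader might infer that all primary events depend on one look at the file. The documents do not support that: peroperative thrombosis is recorded live, observed and volunteered adverse events are recorded in the endpoint's own window, and serious events are reported within 24 hours of staff awareness. This objection stands, and it limits the exposure to non-fatal TEC after discharge.

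**The same-admission window is not contradicted.** A reader might infer that events after day 30 in a long admission are lost. The recording rule names the same admission, an inpatient remains under observation, and a check after 30 days need not fall on day 30 or close the eCRF. Only a clarification is left.

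**Whose file?** The adverse-event section does not say that the file is the trial hospital's own, or that it lacks outside correspondence. That is an inference from collection at each centre. The text supports saying that events can be missed, not that they are.

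**The article is condensed.** The full protocol, the SOPs and the schedule figures are not shown, and a day-30 contact might appear there. This lowers certainty. Still, the method is stated twice rather than left out, and the SOPs are mentioned for proper scoring of data, not for finding events.

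**The size is assumed.** No capture rate is given, equal loss in both arms is an assumption, and no bias between arms is shown. If the planning rates themselves came from similarly incomplete records, they already contain the loss and the power shortfall disappears. This stands as a limit on the calculation.

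**Conclusion.** The concern holds as a gap in post-discharge ascertainment. The article states one active search, in patient files, and describes no query to the patient or to other providers about events. Adjudication works on what the CRF contains.

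The size is modest and conditional. If 5% to 20% of TEC are missed equally in both arms, deaths are complete and the planning rates reflect full capture, the difference falls from 8.0 to between 7.7 and 6.8 points, and power from 80.1% to between 78.2% and 71.6%. If 10% to 30% of TEC occur after discharge and 10% to 50% of those are missed, power lies between 79.7% and 73.9%. No stated figure is wrong, and the 337 and 750 need no change.

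A reader might also apply the loss to every composite event. The documents do not support that, since deaths, live-recorded peroperative events and complications observed in hospital have their own routes.

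This is a cheap improvement worth making while recruitment is early: 90 of 750 patients were included at the time of the article.

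**What to change.** 1. Send every patient a short event block at or just after day 30, through the existing online or postal questionnaire channel. Ask about any admission or visit elsewhere since surgery, and any clot, stroke or TIA, heart attack, or leg or bowel ischaemia. The present 4-week form falls at day 28, before the window closes, and the EQ-5D-5L measures health status, so it does not serve this purpose as it stands.
2. Use admissions reported in the first iMCQ as a back-up. Its date must be settled first: *Follow-up and quality of life measurements* gives 23 weeks, *Cost analysis* gives 13.
3. For each positive answer, obtain the records, enter the event in the CRF and pass it to the blinded adjudication committee.
4. As a minor clarification, state that for patients still admitted at the 30-day check the complication section of the eCRF is completed at discharge, in line with the same-admission window.

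The cost is a small data-handling load and occasional record requests. Form return will be incomplete, so the block supplements the file check and does not replace it. The sample size is unaffected.

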### Inclusion criteria {10}

Inclusion criteria are able to speak and read in the local language of the trial hospital; patients older than 18 years scheduled for elective, open repair of an iliac or abdominal aortic aneurysm distal of the SMA (DSAA segment C); implantation of a tube or bifurcation prosthesis; trans-abdominal or retroperitoneal surgical approach of aneurysm; and able and willing to provide written informed consent.

### Exclusion criteria {10}

Exclusion criteria are not able to provide written informed consent; previous open or endovascular intervention on the abdominal aorta (previous surgery on other parts of the aorta or iliac arteries is not an exclusion criterion); history of coagulation disorders, heparin-induced thrombocytopenia (HIT), allergy for heparin or thrombocyte pathology; impaired renal function with EGFR below 30 ml/min; acute open AAA surgery; hybrid interventions; connective tissue disorders; dual anti-platelet therapy, which cannot be discontinued; life expectancy less than 2 years; inflammatory, mycotic, or infected aneurysms; and allergy for protamine or fish protein.

### Recruitment {15}

Patients scheduled to undergo open AAA repair will be informed about the study by their attending vascular surgeon in the outpatient clinic of participating hospitals about the study and the informed consent procedure will be explained. Informed consent will only be obtained by medical personnel who are GCP licensed. Also, a mandatory training by research staff has to be completed and the site initiation visit (SIV) completed {26a}. This SIV is performed by an external, independent trial research organization: Julius Clinical. A total of 750 patients with an abdominal aortic aneurysm requiring open aneurysm repair will be included in the ACTION-1 study, after signing informed consent (Fig. 1). An EQ-5D-5L questionnaire is handed out to the patient after receiving informed consent. The patient returns the form by post to the investigators, or bring the form when admitted for surgery, for baseline values. Figure 2 shows the participant timeline {13} and Fig. 3 shows the study schedule.

